### Intervention group

Participants in the intervention group will receive EPO Feeding program and standard care. The EPO Feeding program is a 4-module intervention program focused on optimizing parental feeding practices. The components and contents of the EPO Feeding program are presented in Appendix 6. Two healthcare professionals in the Department of Child Health in the local maternal and child health hospital will be trained to deliver the EPO Feeding program. Before each module, they will pre-present the module to the researcher (JW) to ensure their presentation is in accordance with the EPO Feeding intervention manual via VooV Meeting, which will be recorded and sent to parents in the control group after all follow-ups. Considering the effectiveness and cost-effectiveness of the intervention [1], we will divide participants in the intervention group into two groups (15-18 parents per group) to attend the modules separately. Each weekly module will last 45-60 min in the kindergarten classroom, incorporating lesson/session (i.e., slides shows and handouts), group discussion, uptake of key messages, supplementary materials (e.g., stories, key messages and learning videos) to improve the acquisition of participants' knowledge, skills, and behaviors. Each module will take place twice every week (Friday: 12.30-13.30 PM; Saturday: 09.00-10.00 AM) at the kindergarten premises after receiving approval from the gatekeeper. Parents in the intervention group can choose one regular time to attend the module every week. After each module, homework activities will be assigned to participants to help reinforce their knowledge, skills, and behaviors. Participants will receive weekly messages via WeChat reminding them to attend the module with brief information. On the other hand, a WeChat group will be built to facilitate parental involvement, learning, and communication. The WeChat group will be monitored by two healthcare professionals in the areas of child health and nutrition. You can share your feelings, experiences, ideas or practices relevant to each module in the WeChat group. It is

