Quantitative secondary objectives will be addressed using exploratory statistical analysis. Intention-to-treat (ITT) principles will be used for parametric data, with all participants analyzed in the group which they are randomized regardless of whether they attend all data collection time-points or complete the intervention. Multiple imputations by chained equations (MICE) will be adopted to impute missing values if cases with < 10% missing data at each data collection time-point because this procedure can use all available variables with complete information in the study [6]. Descriptive statistics were used to describe the participants' characteristics. The characteristics and all dimensions of outcomes (i.e., parental feeding practices, sense of competence, perception of child weight, and child eating behaviors) will be compared between the intervention group and control group using t-tests (for continuous variables) and chi-squared tests (for categories variables). In addition to the ITT analysis, the completers analysis will be conducted using linear mixed models, which include intervention participants who have completed at least 3 modules (>80% of intervention content) and comparison participants who attend all data collection time-points. The linear mixed model regression procedure will be used to test intervention effects on outcomes with continuous variables. The models will include the outcome measures as the dependent

variables, treatment condition (intervention versus control) as the fixed factor, and confounding factors (e.g., parental education level, children's sex, and age) as covariates. McNemar's Test will be used to test the intervention effect on change in the proportion of parental accurate perception of their preschooler's weight status. Statistical significance is set at  $P < 0.05$  (two-sided). SPSS Statistics 27.0 (IBM Corp, Armonk, NY, USA) will be used for data coding, cleaning, and analysis.

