**(1) Parents in this feasibility trial (including parents in the intervention and control group)**

As this is a feasibility study, a formal sample size calculation for between-group comparisons of a primary outcome is not appropriate. A sample size of between 25 and 50 is considered reasonable in a feasibility study, to be able to establish feasibility, estimate the difference in retention rates with accuracy, and attain an appropriate standardized effect size (0.15-0.3) [1, 2]. The target recruitment for this feasibility RCT will be 70 (i.e., 35 participants per group), allowing for a 20% loss to follow-up rate and for at least 56 participants to complete the study.

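### The tests of effect treat all parents as independent, although the intervention arm is taught in two separate discussion groups; if session-mates' outcomes are correlated, the standard errors are too small

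*Protocol*

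**What the plan says.** Parents are randomized individually, 1:1 (Protocol B9, Randomization). On size, C1 states: "The target recruitment for this feasibility RCT will be 70 (i.e., 35 participants per group"). That total assumes that a fifth of the parents are lost, which leaves 56 completers. The same section says that "a formal sample size calculation for between-group comparisons of a primary outcome is not appropriate".

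Delivery differs between the arms. Under B9, Intervention group, the plan is that "we will divide participants in the intervention group into two groups (15-18 parents per group) to attend the modules separately", with group discussion as part of each weekly module, and that "Parents in the intervention group can choose one regular time to attend the module every week". Under B9, Control group, control parents receive printed standard-care material and no sessions until the last follow-up is over.

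Under B9, Quantitative data analysis, parent characteristics and all outcome dimensions are compared between arms by t-tests and chi-squared tests. A linear mixed model tests intervention effects on continuous outcomes, with "treatment condition (intervention versus control) as the fixed factor, and confounding factors (e.g., parental education level, children's sex, and age) as covariates". The threshold reads "Statistical significance is set at $P < 0.05$ (two-sided"). The analyses of the secondary objectives are labelled exploratory. Clustering by session group is not mentioned anywhere in the Protocol.

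**The concern.** This is a partially nested design: randomization is by individual, but from the first module onwards the intervention parents share a room, a discussion and a particular delivery of the material, and the controls do not. Anything that happens in one session group and moves its members together adds variance to the intervention mean that does not shrink as parents are added; it shrinks only as groups are added, and there are two. A t-test or chi-squared test estimates its standard error from the spread between parents and does not see that component. How two particular sessions happened to go can then pass for an effect of the programme.

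Estimating potential effects is a stated objective, and the trial is meant to prepare for a full trial. Effect estimates that look more precise than they are would be carried into that planning.

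**Working it through.** **Inputs.** From the Protocol: 70 recruited, 35 per arm; 20% loss; at least 56 completers (28 per arm if loss is equal); two intervention groups of 15-18; two-sided 0.05. Assumed, because the documents give none: the ICC within session groups, over 0 to 0.10.

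**The plan's own figure.** 56 / (1 - 0.20) = 70, as stated. The group sizes also fit: 2 x 15 to 2 x 18 gives 30 to 36 parents, and 35 / 2 = 17.5 on average.

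**Formulas.** Total variance is 1 in each arm; correlation exists in the intervention arm only.
- Intervention-arm design effect: D = 1 + (m - 1) x ICC
- True SE / SE from the planned test: R = sqrt((D + 1) / 2)
- Actual two-sided error: 2 x (1 - Phi(1.96 / R))

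**Example, ICC 0.05, m = 17.5.** D = 1 + 16.5 x 0.05 = 1.825. R = sqrt(2.825 / 2) = 1.188. 1.96 / 1.188 = 1.65, giving an error of 0.099.

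| ICC (assumed) | D (35 per arm) | R | Error, formula | Error, simulated | Effective intervention n | Error, formula, 28 per arm |
|---|---|---|---|---|---|---|
| 0 | 1.000 | 1.000 | 5.0% | 5.0% | 35.0 | 5.0% |
| 0.01 | 1.165 | 1.040 | 6.0% | 5.9% | 30.0 | 5.8% |
| 0.02 | 1.330 | 1.079 | 6.9% | 6.9% | 26.3 | 6.5% |
| 0.05 | 1.825 | 1.188 | 9.9% | 10.0% | 19.2 | 8.9% |
| 0.10 | 2.650 | 1.351 | 14.7% | 15.0% | 13.2 | 12.7% |

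The simulations apply a two-sample t-test to groups of 18 and 17 against 35 independent controls, with no effect on average over groups (200,000 trials per setting; 40,000 at ICC 0.02).

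**Width of an interval.** At 35 per arm, the independent-observations half-width is 1.995 x sqrt(2/35) = 0.477 SD. With the ICC treated as known, it becomes 0.477 x 1.188 = 0.57 SD at ICC 0.05 and 0.477 x 1.351 = 0.64 SD at ICC 0.10. If the between-group variance has to be estimated from the two groups, only about 2.4 and 1.9 Satterthwaite degrees of freedom remain, and the half-width is about 1.06 and 1.47 SD. Two groups cannot supply a usable ICC estimate.

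**Does choosing one's own slot add to this?** No. Choice follows randomization, so it only re-sorts 35 independent parents, and the variance of the whole-arm mean does not depend on how they are split. In a simulation (100,000 trials per setting), parents were sorted into slots by a trait correlated 0.2, 0.3 or 0.4 with the outcome. The apparent ICC was 0.05, 0.11 and 0.18, yet rejection stayed at 5.0%, 5.0% and 5.1%.

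**The case against.** The strongest reply is that the inflation depends on an unstated correlation and on which null is meant. If the programme changes nobody's outcome, discussion creates no correlation, and individual randomization keeps the test near 5%. That stands. The error rates above refer to group effects that are real but average to zero over groups, which is the relevant null for whether an effect would recur in new groups.

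Other points also stand:
- The groups are not rigidly fixed. Section D1d (ii) lets parents attend Friday or Saturday as convenient, and one WeChat group serves the whole arm. Switching and arm-wide contact would dilute a session-group correlation, though not necessarily remove it.
- The random part of the mixed model is not stated, and a statistical analysis plan could add a group term. A reader might infer that the model is certain to ignore the groups; the Protocol shows only that none is named. The t-tests and chi-squared tests cannot take such a term.
- The sentence on those tests gives no time point and might be read as a baseline comparison. But the Protocol next introduces the completers analysis as an addition to the ITT analysis, which suggests that the tests before it are the ITT comparison.
- McNemar's test is a paired before-after test and is not the target here.

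A reader might also infer that the trial's confidence intervals are too narrow. The analysis section plans none, so that applies only to intervals that someone builds from these tests, and only if the ICC is above 0.

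**Conclusion.** The point holds conditionally. The named t-tests and chi-squared tests assume independence that the delivery format puts in doubt in one arm. With 35 per arm, the standard error is too small by a factor of 1.04 at ICC 0.01, rising to 1.35 at ICC 0.10, and the actual error runs from about 6% to about 15%. At ICC 0.01-0.02 the effect is small, and at ICC 0 there is none. These figures rest on an assumed ICC, equal total variance in the arms and stable session groups.

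Three stronger conclusions are not supported. The documents do not show that false positives will exceed 5%, because they give no ICC. Similarity within a session that comes from parents choosing the same slot does not inflate the error. And the primary feasibility and acceptability results, which are descriptive, do not depend on these tests. This is a worthwhile and cheap correction to an exploratory secondary analysis, not a flaw in the trial's main purpose.

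**What to change.** In B9, Quantitative data analysis:

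1. Record the session slot of each intervention parent. The Attendance/Adherence list in B8 counts modules and homework and does not mention the slot.
2. Show each outcome for the two session groups separately, beside the control arm.
3. Present the exploratory effects as differences with 95% intervals. Add a sensitivity analysis that multiplies the intervention-arm variance by 1 + (m - 1) x ICC at ICC 0, 0.02, 0.05 and 0.10, where m is the session-group size, for means and proportions alike.
4. State that two groups are too few to estimate the ICC, that these intervals treat it as known, and that P < 0.05 from the unadjusted tests is not to be read as evidence of effect.
5. Carry the same ICC range into the sample size of the full trial.

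No single ICC should serve as a cut-off for calling a result a signal; the documents offer no basis for one, and the range is what informs the reader.

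Cost: one extra variable and a few table rows, with no added participants or staff. At 35 per arm the intervals are about 19% wider at ICC 0.05 and 35% wider at ICC 0.10, so fewer exploratory results will look conclusive.

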### Study design

EPO Feeding program involves several components, targeting optimizing parental feeding practices in China. A two-arm feasibility and acceptability RCT with three repeated measures will be used to test the feasibility and acceptability of EPO Feeding program. After baseline assessment, parents who are responsible for their child's eating behaviors and family food environment will be randomly assigned to one of the two conditions: one experimental group (EPO Feeding program and standard care) and one control group (standard care). The four weekly modules of the multicomponent intervention curriculum include four modules. After finishing the program, parents complete the measures immediately and one-month follow-up. Semi-structured interviews will be conducted with parents to support the process evaluation of the 4-week intervention program after the intervention.

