### Randomization

The randomization will be performed by an independent researcher (XXW) not connected with either participant recruitment or data collection. After completing the baseline assessment, parents will be randomized and allocated to one of the conditions through a concealed computerized random number generator by randomization.com, with an equal allocation ratio (1:1). Selection bias will be minimized by ensuring all participants eligible and recruited have equal opportunity of being allocated to each study group and follow-up completed. Due to the nature of the study, only the research members who collect and analyze the data from participants can be masked to the randomization. At the follow-up data collection time points, child height and weight measurements, and follow-up questionnaires will be taken and distributed by a trained kindergarten healthcare staff blinded to group allocation. Unmasking will not occur until databases are closed, and the main analysis has been completed.

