##### - Quantitative data

Demographic and socioeconomic data including children's age, sex; caregivers' role, age, weight, height, education level and household annual income, and number of children will be collected at baseline only. A survey related to the trial acceptability will be assessed immediately after the intervention (Appendix 7). Quantitative data including parental feeding practices, perception of child weight, parenting sense of competence; and child eating behaviors will be collected from participants at three-time points: baseline (T0), immediately after the intervention (T1), and one month after the intervention (T2). The kindergarten healthcare staff who is unaware of participants' group allocation will be trained to distribute and collect the questionnaires and measure children's weight and height at each time point in the kindergartens. The questionnaire will take approximately 15 minutes.

The questionnaire also includes some identified information: preschool child student ID number, participant contact details (phone number). We need to assess child's actual weight and height at the kindergarten at each time point after getting the approval of kindergarten gatekeeper. Except for baseline assessment (T0), parents in the intervention group will receive text messages about their preschool child's actual weight status a week before the assessment of each time point from a kindergarten healthcare staff who is not involved in collecting child weight and height and is not blind to group allocation. We will also use child's actual weight status to compare with parental self-reported and visual perception of child's weight separately and then, we can calculate the prevalence of parental misperception of child's weight in this sample.

The included scales have been all used in the Chinese sample and showed moderate to good internal consistency reliability in existing studies including my previous study [2]. The questionnaire is attached in the additional file (Appendix 4 and 5).

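### The mixed model names no visit, arm-by-visit or baseline-outcome term, so it cannot give separate T1 and T2 effects, and it understates the effect if T0 is among the outcomes

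*Protocol*

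**What the plan says.** Protocol B9, Study design: "A two-arm feasibility and acceptability RCT with three repeated measures will be used". B9, Data collection (Quantitative data) places these at baseline (T0), straight after the programme (T1) and one month later (T2). B9, Randomization: "After completing the baseline assessment, parents will be randomized and allocated to one of the conditions". T0 is therefore a pre-randomisation measurement.

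B9, Quantitative data analysis, describes two analyses of the continuous outcomes.

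- Participant characteristics and the outcome dimensions "will be compared between the intervention group and control group using t-tests". No visit is named.
- A linear mixed model is introduced with the completers analysis: intervention parents with at least three modules, and comparison parents present at every data collection. The text continues: "The linear mixed model regression procedure will be used to test intervention effects on outcomes with continuous variables". The terms are the outcome measures as dependent variables, "treatment condition (intervention versus control) as the fixed factor, and confounding factors" as covariates, with parental education and the child's sex and age as examples.

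The protocol does not say which visits supply the outcome rows.

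**The concern.** The model has one design factor, treatment, for data collected at three visits. If all three visits are outcome rows, the treatment coefficient is a weighted average of the arm differences at T0, T1 and T2. In the randomised set the T0 difference has expectation zero, so including it pulls the estimate towards zero. If T0 is left out, the model as listed does not use the baseline score, usually a strong predictor of the follow-up score. In both cases a single treatment coefficient cannot show whether an immediate effect persists at one month.

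Testing potential effects is the second stated objective (B5), and the study prepares for a full trial (B8, Process evaluation). A shrunken estimate carried into that trial would matter: with all else equal, planning on 0.20 SD when the truth is 0.30 SD multiplies the sample size by (0.30/0.20)² = 2.25.

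**Working it through.** **Inputs from the protocol.** Three visits, with randomisation after T0; 1:1 allocation; 70 recruited, 20% loss, 56 completing (C1); two-sided 5% level (B9); and the only standardised effect size mentioned, 0.15–0.3 (C1).

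**Assumptions (the protocol gives no values).** Within-person correlation r; SD 1 at each visit; a constant effect d at T1 and T2; d = 0.5 as an illustration beside d = 0.3. Demographic covariates are left out of all the comparisons.

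**The plan's own figure.** 56/(1 − 0.20) = 70, and 70 × 0.80 = 56, so 28 per arm complete. This reproduces. It does not depend on the model, because C1 makes no between-group calculation.

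**What the coefficient estimates if T0 is an outcome row (randomised set).** The arm differences are (0, d, d).

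- Compound symmetry (random intercept): weights are 1/3 each at any r, so the coefficient estimates (0 + d + d)/3 = 0.667d. A true 0.3 appears as 0.20 and a true 0.5 as 0.33.
- AR(1): weights are proportional to (1, 1 − r, 1), so the coefficient estimates d(2 − r)/(3 − r). At r = 0.3 this is 1.7/2.7 = 0.63d; at r = 0.8 it is 1.2/2.2 = 0.55d.

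**The same in the completers set.** The T0 difference need not be zero. If it is b, and the later difference in that set is d, compound symmetry gives (b + 2d)/3. The distortion then depends on b and is not fixed at one third.

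**Precision.** Compound symmetry, r = 0.6, variances as multiples of 2/28 = 0.0714:

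- Three visits, treatment only: (1 + 2r)/3 = 0.733; SE = √(0.0714 × 0.733) = 0.229.
- T1 and T2, no baseline: (1 + r)/2 = 0.80; SE = 0.239.
- T1 and T2, adjusted for baseline: (1 + r)/2 − r² = 0.80 − 0.36 = 0.44; SE = 0.177.

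**Illustrative power**, Φ(estimated effect/SE − 1.96):

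| Model | d = 0.5 | d = 0.3 |
|---|---|---|
| T0, T1, T2, treatment only | 0.333/0.229: 31% | 0.20/0.229: 14% |
| T1, T2, no baseline | 0.5/0.239: 55% | 0.3/0.239: 24% |
| T1, T2, baseline-adjusted | 0.5/0.177: 80% | 0.3/0.177: 39% |

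**Simulation check.** In 300 simulated trials with a random-intercept model (d = 0.5, r = 0.6, 28 per arm), the mean coefficient was 0.34 with T0 included and treatment only, against 0.51 with T1 and T2 adjusted for baseline. Rejection rates were 35%, 55% and 82% in the order of the table.

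**The case against.** A reader might infer more than the documents support, in five ways.

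- *That the effect will certainly be diluted.* The protocol never says that T0 is an outcome row. If only T1 and T2 are modelled there is no dilution. This objection stands, so the two-thirds figure is conditional.
- *That the intention-to-treat analysis is biased too.* The t-test sentence names no visit and may partly describe a baseline comparison. If it is the outcome test, a t-test at T1 or at T2 between randomised arms is unbiased and specific to that visit. Its weakness is efficiency only.
- *That adjusting for education, sex and age is an error because randomisation balances them.* The mixed model is introduced for a completers set chosen by different rules in each arm, where confounding can return. Adjustment for prognostic covariates is acceptable in the full set as well.
- *That an adequately powered test is being lost.* The 80% figure needs d = 0.5, above the protocol's 0.15–0.3. C1 says that a formal between-group sample size calculation is not appropriate here, so power is not a design criterion.
- *That this undermines the trial.* The primary objectives are feasibility and acceptability, analysed descriptively.

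It can also be said that B9 is a lay-language ethics answer, that model detail belongs in an analysis plan, and that the covariate list is open-ended. The last point has force for the baseline score, which is not expressly excluded. It has none for visit or arm-by-visit, which are not confounders. The protocol does not leave the model open: it lists the terms, and with those terms the model gives no visit-specific post-intervention effect.

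**Conclusion.** The point holds with moderate severity. As listed, the mixed model cannot give separate T1 and T2 effects, whichever visits enter it. If T0 is an outcome row, the coefficient in the randomised set estimates 0.67 of a constant effect under compound symmetry, or 0.55–0.63 under AR(1) with correlation 0.8–0.3. In the completers set the size of the distortion cannot be fixed in advance. If T0 is not an outcome row, the loss is one of precision, an SE about 35% larger (0.239/0.177 = 1.35) at r = 0.6, unless the baseline score is added under the open covariate list. The correlations and d = 0.5 are assumptions. The power figures only illustrate; the main harm is a possibly understated effect estimate carried into the planning of a full trial.

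**What to change.** For the continuous outcomes, replace the list of model terms in B9 with the following.

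- Population: all randomised participants.
- Outcome rows: T1 and T2.
- Fixed effects: arm, visit, arm-by-visit and the baseline value of the same outcome. The demographic covariates may stay.
- Within-person correlation: a participant random intercept or an unstructured covariance.
- Report: the arm difference at T1 and at T2, each with a 95% CI.

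A constrained longitudinal model, with T0 as an outcome and a common T0 mean, is an equivalent choice in the randomised set. Use this model as the intention-to-treat effect analysis in place of the unadjusted t-tests. Use the same fixed effects in the completers analysis, with baseline as a covariate, because a common T0 mean is not assured there.

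The cost is wording only, settled before unmasking. Every variable is already collected, and the sample size does not change.
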